## Abstract

**Background:**

Radiation therapy is an integral part of the multimodal primary therapy of glioblastomas. As the overall prognosis in this tumor entity remains unfavorable, current research is focused on additional drug therapies, which are often accompanied by increases in toxicity. By using proton beams instead of photon beams, it is possible to protect large parts of the brain which are not affected by the tumor more effectively. An initial retrospective matched-pair analysis showed that this theoretical physical benefit is also clinically associated with a reduction in toxicity during therapy and in the first few months thereafter.

**Methods/design:**

The GRIPS trial is a multicenter, prospective, open-label, randomized, two-arm, phase III study using either intensity modulated photon radiation techniques (standard arm) or proton beam radiotherapy (experimental arm). Additionally, patients are stratified according to "fractionation scheme" (normofractionated/hypofractionated), "subventricular zone involvement" (yes/no) and concurrent chemotherapy (yes/no) and the planned case number is 326 patients.

Radiation therapy is performed with a dose of 30 × 2 Gy(RBE) or 33 × 1.8 Gy(RBE), or for patients treated according to the hypofractionation protocol with 15 × 2.67 Gy(RBE). A possible administration of additional chemotherapy (concurrent or adjuvant) or tumor treating fields is applied in dosage and frequency according to the therapy standard outside of this study. The primary endpoint is the cumulative rate of toxicity CTC grade 2 and higher in the first 4 months. Secondary endpoints include overall survival, progression-free survival, quality of life, and neurocognition.

**Discussion:**

Aim of the GRIPS study is to prospectively assess whether the theoretical physical advantage of proton beam radiotherapy will translate into a clinical reduction of toxicity during and in the first months after therapy.

*Trial registration*

ClinicalTrials (NCT): NCT04752280.

## Background

In treatment of glioblastoma patients complete resection of the tumor should be attempted whenever possible. This should be followed by adjuvant radiotherapy up to a dose of 60 Gy and concurrent chemotherapy with temozolomide (75 mg/m^2^ KOF; daily during the radiation period) and further adjuvant chemotherapy with temozolomide (6 cycles of 150 or 200 mg/m^2^ KOF each for 5 days every 4 weeks). If surgery is not possible, the aforementioned radiochemotherapy is applied as definitive therapy.

A treatment which was investigated in the EORTC-NCIC trial but that also showed that the prognosis of glioblastoma is very unfavorable with a median survival of 14.6 months [1]. Furthermore, Glioblastomas that involve the subventricular zone appear to have a particularly unfavorable prognosis, as these have a higher risk of multifocal/distant progression [2].

Patients with a methylated MGMT promoter appear to benefit from additional administration of lomustine to radiochemotherapy with temozolomide, which significantly increased median survival in the CeTeG study up to 48.1 months [3].

While great efforts are being made to achieve treatment optimization on the drug side, radiotherapy as a standard therapy has not changed significantly in recent decades, apart from a reduction in treatment time in elderly patients with glioblastomas [4]. However, radiotherapy remains an integral part of the primary treatment of glioblastoma.

Proton beams, which have a steeper dose gradient compared to (conventional) photons, can therefore be applied in a more concentrated manner with significantly lower dose exposure outside the irradiated volume. This physical advantage could be demonstrated for higher-grade gliomas and glioblastomas in a plan comparison study [5]. Additionally, in a matched pair analysis of the Heidelberg patient collective with 66 patients with higher-grade glioma or glioblastoma who had received part of the irradiation with protons (10 Gy proton boost after 50 Gy photons) were compared with a corresponding cohort, who had received the entire irradiation with photons. While identically effective, there was a trend towards increased toxicity in the group treated only with photons over the therapy period and the first 3 months thereafter (toxicity grade 2/3: photons: 14 patients, photons + protons 6 patients; *p* < 0.1), whereas grade 3 toxicities occurred only in the group with photon therapy alone [6].

A reduction in irradiated brain volume may also affect the number of circulating lymphocytes. A recently published randomized phase II trial reduced the likelihood of high-grade radiation-induced lymphopenia in glioblastoma patients when using proton beam therapy compared to photon irradiation [7]. This might also influence survival due to higher probability of implementation of concurrent and adjuvant chemotherapy regimens.

Aim of the current study is to prospectively evaluate if the theoretical physical advantage of proton beam radiotherapy will translate into a clinical reduction of toxicity during and in the first months after therapy compared to classical photon irradiation without compromising efficacy in patients with glioblastoma.

## Methods/design

### Study design

The study is a multicenter, prospective, open-label, randomized, two-arm, phase III study, which will be conducted at 3 locations in Germany (Heidelberg, Marburg/Gießen, Stuttgart).

### Objectives

Patients in the study will be treated either by modern intensity modulated photon irradiation (IMRT) technique (standard arm) or by proton beam radiotherapy (experimental arm). The aim of the GRIPS study is to prospectively test if the theoretical physical advantage of proton beam radiotherapy will translate into a clinical reduction of toxicity during and in the first months after therapy.

### Endpoints

The primary endpoint is the cumulative rate of toxicity CTCAE ≥ grade 2 in the first 4 months. Secondary endpoints are progression-free survival (secondary endpoint of special interest), overall survival, acute and late toxicity, quality of life and neurocognition.

### Additional scientific program

The influence of the irradiation technique on the lymphocyte count will be evaluated in an additional scientific program.

### Inclusion criteria

Patients (Age ≥ 18 years, ECOG 0–2) with histologically confirmed glioblastoma (WHO grade 4) with indication for radiotherapy/chemoradiation.

### Exclusion criteria

Patients who are not capable of giving consent, previous radiation therapy to the brain or skull base, active medical implants for which no approval for ion irradiation exists at the time of treatment (e.g., pacemaker, defibrillator, etc.), contraindication to MRI imaging, concurrent participation in another clinical trial that could affect the results of this trial or the other trial.

### Randomization

Screened and eligible patients will be enrolled into the study after study initiation. To obtain similar distribution of prognostic variables in both treatment groups, each patient will be randomly assigned to treatment groups (1:1) in balanced permuted blocks. Stratification according to "fractionation scheme" (normofractionated/hypofractionated), "subventricular zone involvement" (yes/no) and concurrent chemotherapy (yes/no) will be applied using the web-based software randomizer.at (provided by the Institute of Medical Informatics, Statistics and Documentation of the Medical University of Graz (https://www.randomizer.at)). According to case number planning, 326 patients should be randomized, see Fig. 1.

**Fig. 1 Fig1:**
[figure not shown]
Flow diagram of the process of the study phases of the GRIPS trial. IMRT = intensity-modulated radiotherapy, RT = radiotherapy

### Target volume delineation and radiotherapy application

The patient is positioned using a suitable fixation method (e.g. thermoplastic mask). Computed tomography must be performed natively in 3 mm slice thickness or less and, if possible, also with contrast medium.

Target volume definition will be performed according to the ESTRO-ACROP guideline and additional MRI sequences [8]:GTV: contract-enhancing macroscopic tumor and/or resection cavity with contrast-enhancing residual tumor parts, taking into consideration planning MRI with preoperative scans and early postoperative imaging to prove for more precise delineationCTV: is defined as the GTV plus a 1.5–2.0 cm margin to account for microscopic spread. It should be defined considering anatomical borders and inclusion of abnormal (postoperative) T2-FLAIR signalPTV: CTV + 3 mm

In cases where the CTV accounts for > 25% of the total brain volume, a boost volume should be defined after 50 Gy, which covers only the GTV + 1.5–2 cm (without further consideration of abnormal T2-FLAIR signal).

Organs at risk (OAR) definitions and dose limitations for OARs are chosen according to table 2 of Niyazi et al. [8]. Expansion of OARs to create a planning risk volume (PRV) for OAR is applied when necessary and the margin should reflect the accuracy of daily set-up.

Photon radiotherapy is performed in all participating centers, while proton beam radiotherapy is performed at the Heidelberg ion beam therapy center (HIT) or Marburg ion beam therapy center (MIT) with 5 fractions per week. The applied dose is 30 × 2 Gy(RBE) or 33 × 1.8 Gy(RBE), or for patients treated according to the hypofractionation protocol ((4, 11)) due to age or comorbidities, with 15 × 2.67 Gy(RBE), all prescribed to the PTV. The dose to the PTV should be homogenous, with at least 95% of the PTV covered by the 95% prescription isodose, and dose maximum less than 107% of the prescribed dose (according to the ICRU 62 and 93 [9, 10]). Photon radiotherapy in the standard arm must be applied as IMRT. Treatment is applied with image guidance with frequency according to the location of the target volume, setup and/or the treating physician´s choice. Figure 2 shows an example of the dose distribution of a representative patient case comparing IMRT and proton radiotherapy.

**Fig. 2 Fig2:**
[figure not shown]
Representative transversal images show the IMRT plan (**A**) and the proton plan (**B**) of a patient with glioblastoma of the right temporal lobe. The DVH shows some of the relevant organs at risk in corresponding colors in solid and dashed lines, for IMRT and proton beam radiotherapy, respectively. While the PTV (red) coverage is similar in both techniques, dose to the surrounding organs is reduced in the proton plan

A possible administration of additional chemotherapy (concurrent or adjuvant) as well as tumor treating fields is applied in dosage and frequency according to the therapy standard outside of this study. The subject of the examination within this trial is only the different radiation quality.

### Timeline of the study

The number and content of clinical visits correspond to those of standard therapy. The study-related additional effort results from the testing of neurocognition by means of the Hopkins Verbal Learning Test (HVLT-R; [11, 12]) and the regular completion of the quality-of-life questionnaires. The timeline with its different examinations is displayed in Table 1. Oncological follow-up begins 4 weeks after the end of radiotherapy. Further follow-up appointments are month 4, month 7, and subsequently every 3 months until month 25 (Table 1).

**Table 1 Tab1:** Intervention and assessment schedule for the GRIPS trial

	Inclusion examination	RT	Examination after RT	V1: 4 weeks after RT	V2: month 4	V3: month 7	V4: month 10	V5: month 13	V6: month 16	V7: month 19	V8: month 22	V9: month 25
Screening	x											
CRF form	x		x	x	x	x	x	x	x	x	x	x
QLQ-C30 und QLQ-BN20	x		x		x			x				
Hopkins Verbal Learning Test- Revised	x		x		x			x				
Symptoms/ Toxicity according to CTCAE	x		x	x	x	x	x	x	x	x	x	x
MRI	x^a^			x	x	x	x	x	x	x	x	x
RT		x										
Additional scientific program	x		x	x	x							

RT = radiotherapy

Screening: includes check of inclusion and exclusion criteria, taking of medical history including surgical and pathological report, medical examination and randomization

^a^ MRI less than 4 weeks old, if older at time of inclusion, a new MRI for planning is mandatory

Patients will be recruited over a period of 4 ¼ years, and the evaluation of the study results regarding the primary endpoint of the study (toxicity grade ≥ 2) will be evaluated 4 months after the end of radiation of the last patient. The end of the study is defined as the end of the follow-up period of the last patient (25 months after start of treatment).

### Assessment of safety, toxicity and neurocognition

Acute and late radiotherapy toxicity will be assessed closely during and after therapy at each follow-up appointment using the NCI CTCAE version 5.0 criteria, quality of life will be measured using the EORTC questionnaires QLQ-C30 and QLQ-BN20. Neurocognition will be tested using Hopkins Verbal Learning Test-Revised.

### Radiological assessment

Response assessment is evaluated primarily radiologically according to the RANO criteria, see Table 1 of the publication by Wen et al. [13]. Tumor progression is defined as a new contrast uptake outside of the radiation field (beyond the high-dose region or 80% isodose line) or at least a 25% increase in tumor volume (product of two diameters perpendicular to each other). Pseudoprogression is defined as contrast uptake in the first 3 months after radiotherapy if it stabilizes on subsequent MRI scans, according to table 2 by Wen et al. [14]. Newly appeared contrast uptake originating from the ventricular zone and not located in the area of the initial contrast uptake is primarily defined as radiogenic blood brain barrier disruption. If a lesion initially defined as a pseudoprogression or as a radiogenic barrier disruption, which may turn out to be a disease progression in the further course, the date of progression is backdated. All follow up MRIs are reviewed centrally.

### Statistical considerations

The primary study objective is to demonstrate that the toxicity rate (rate of CTCAE toxicity grade ≥ 2) under proton therapy, π^Pr^, is lower than the toxicity rate under photon therapy, π^Ph^. Thus, the null hypothesis of the study is that the toxicity rate in the proton group is greater than or equal to the toxicity rate in the photon group, i.e., H_0_: $${\pi }_{A}^{Pr}\ge {\pi }_{A}^{Ph}$$. For sample size planning, rates of $${\pi }_{A}^{Ph}=21\%$$ for the photon group and $${\pi }_{A}^{Pr}=9\%$$ for the proton group were assumed under the alternative hypothesis. This assumption results from a matched-pair analysis of the Heidelberg patient collective [6]. Under these assumptions, 276 evaluable patients (138 per group) are needed to reject the null hypothesis with a power of 1-β = 80% using the chi-square test at the one-sided significance level α = 0.025. Assuming a dropout rate of 15%, 326 patients (163 per group) will be included in the study. In the analysis, a logistic regression model will be applied for the evaluation of the primary endpoint adjusting for the confounders "fractionation," "subventricular zone involvement", and "concurrent chemotherapy". It is expected that this will increase power as compared to using the chi-square test. The secondary variables will be evaluated with methods of descriptive data analysis.

The intention-to-treat (ITT) population is the primary evaluation population for all efficacy endpoints and patient characteristics. The ITT population comprises all randomized patients which are evaluated in the treatment arm to which they were randomized. The per-protocol (PP) population includes all patients in the ITT population who received the planned therapy in its entirety and for whom documentation is complete with respect to the primary endpoint. The analyses of the PP population serve as sensitivity analyses, which will be used to investigate the robustness of the results from the ITT analysis. All patients in the ITT population in whom the planned therapy was started (at least 1 day) belong to the safety population and will be evaluated in the therapy arm to which they were treated. This is the primary evaluation population for the primary endpoint as well as for all other safety endpoints.

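### The per-protocol set requires full receipt of planned therapy, so for the toxicity endpoint it drops patients whose therapy was stopped by the event itself; the bias can go either way

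*Protocol article*

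**What the plan says.** All of this is in the Protocol article.

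- **Endpoint** (Endpoints): "The primary endpoint is the cumulative rate of toxicity CTCAE ≥ grade 2 in the first 4 months".
- **Per-protocol set** (Statistical considerations): patients of the ITT population "who received the planned therapy in its entirety and for whom documentation is complete with respect to the primary endpoint". No exception is made for patients who stopped because of toxicity.
- **Its purpose** (same section): "The analyses of the PP population serve as sensitivity analyses, which will be used to investigate the robustness of the results from the ITT analysis".
- **Safety population** (same section): "All patients in the ITT population in whom the planned therapy was started (at least 1 day) belong to the safety population", analysed by the treatment received. Of this set the section says: "This is the primary evaluation population for the primary endpoint as well as for all other safety endpoints".
- **Model** (same section): logistic regression adjusted for the three stratification factors. The planning rates are 21% (photon) and 9% (proton).

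**The concern.** Whether a patient completes therapy is known only after randomisation, and the primary event can itself prevent completion. A rule that demands completion therefore selects on the outcome: it removes some patients with the event for a reason that patients without the event cannot have.

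What is at stake is how the robustness check is read. If the per-protocol and primary toxicity results disagree, the reader cannot tell real fragility from exclusions driven by the outcome. If they agree, the agreement is also hard to interpret. Both the definition and its purpose are written out in the article, so this is a stated rule and not a detail left to an analysis plan.

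The wording also ties the check to the ITT result, whereas the primary set for this endpoint is the safety population.

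**Working it through.** **1. The plan's own figure.** Inputs from Statistical considerations: 21% vs 9%, one-sided alpha 0.025, power 80%, chi-square test, 1:1 allocation. With pooled variance and no continuity correction, the mean rate is 0.15 and

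n = [1.960·√(2·0.15·0.85) + 0.842·√(0.21·0.79 + 0.09·0.91)]² / 0.12² = (0.990 + 0.419)² / 0.0144 ≈ 137.8, so 138 per group and 276 in total.

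Dropout: 138/0.85 = 162.4, so 163 per group and 326 in total. Both stated figures reproduce. No planning number is wrong.

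**2. Effect of the exclusion.** Let p be the true event rate and s the share of patients with an event who do not complete planned therapy because of it. The documents give no value for s, so every value below is an assumption. Non-completion for other reasons is taken as unrelated to the outcome and left out.

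- Per-protocol rate = p(1−s) / (1−ps).
- Per-protocol odds = p(1−s) / (1−p).
- Hence per-protocol odds ratio = true odds ratio × (1−s photon) / (1−s proton).

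The true odds ratio at the planning rates is (0.21/0.79) / (0.09/0.91) = 2.69. The direction of bias depends only on which arm has the larger s.

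| s photon / s proton (assumed) | Per-protocol rates | Difference (points) | Odds ratio |
|---|---|---|---|
| 0% / 0% | 21.0% vs 9.0% | 12.0 | 2.69 |
| 10% / 10% | 19.3% vs 8.2% | 11.1 | 2.69 |
| 20% / 20% | 17.5% vs 7.3% | 10.2 | 2.69 |
| 30% / 30% | 15.7% vs 6.5% | 9.2 | 2.69 |
| 30% / 10% | 15.7% vs 8.2% | 7.5 | 2.09 |
| 50% / 10% | 11.7% vs 8.2% | 3.6 | 1.49 |
| 0% / 30% | 21.0% vs 6.5% | 14.5 | 3.84 |

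Worked example, 30% / 10%: 0.21·0.7 / (1 − 0.063) = 0.157; 0.09·0.9 / (1 − 0.009) = 0.082; 2.69 × 0.7/0.9 = 2.09.

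**3. No true difference.** With 21% in both arms and s = 10% photon / 30% proton, the per-protocol rates are 19.3% vs 15.7%. Starting from 138 per group, the one-sided test then rejects about 12% of the time instead of 2.5%.

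**4. Would waiving the documentation condition for patients with an event help?** No. That keeps every event and drops incompletely documented non-events. If 15% of non-events are incomplete (an assumption), 21% becomes 0.21 / (0.21 + 0.79·0.85) = 23.8% and 9% becomes 0.09 / (0.09 + 0.91·0.85) = 10.4%. Both rates are inflated, and the gap widens from 12 to 13.4 points.

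**The case against.** The strongest reply is that the main analysis is already protected. The safety population needs only that therapy was started, so patients stopped by toxicity stay in the primary analysis of the primary endpoint. That stands in full and limits the point to a supportive analysis.

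Other parts of the reply also stand:

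- **Few patients may be affected.** The article says that the trial examines only the radiation quality (under Fig. 2), so planned therapy most naturally means radiotherapy: 15 to 33 fractions at 5 per week, or 3 to 6.6 weeks. Events after that cannot prevent completion, and patients with toxicity who finish treatment remain in the set.
- **Scope.** The text links the per-protocol check to the ITT result, and ITT is the primary set for efficacy endpoints. That the check also covers toxicity is inferred from the reference to primary-endpoint documentation in the definition. The analysis plan, not shown, may add further analyses.
- **Documentation.** The condition does not explicitly require a month 4 visit. A recorded event may already satisfy it.

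A reader might infer three stronger things that the documents do not support:

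- *That the check is useless.* With equal stopping shares the odds ratio, the scale of the planned logistic model, does not move.
- *That it must understate the proton benefit.* The difference in rates does shrink with equal shares, but unequal shares can shift the contrast in either direction.
- *That photon losses would be larger.* The Background does report that "grade 3 toxicities occurred only in the group with photon therapy alone". But this comes from a retrospective matched-pair comparison in which the proton patients had 50 Gy of photons followed by a 10 Gy proton boost, and it gives no data on stopping treatment.

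Loss of power in the per-protocol set (for example, 72% at 20% / 20%) carries little weight, because no power target is set for that set.

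**Conclusion.** The point holds as a defect in a supportive analysis. For a toxicity endpoint, a set defined by completed therapy removes patients because of the outcome. This biases the per-protocol rates downward and, if stopping differs by arm, biases the contrast in either direction. In the scenarios shown the odds ratio runs from 1.49 to 3.84 against a true 2.69. This range illustrates the mechanism and does not forecast the trial, since it rests wholly on assumed stopping shares. The primary analysis, the sample size of 326 and alpha are unaffected. The change is worth making because it is cheap and because the check as defined cannot be read clearly whichever way it comes out.

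**What to change.** Amend the population definitions for the primary endpoint before the analysis:

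1. Do not treat non-completion of therapy because of toxicity as a per-protocol deviation. Keep these patients with their observed outcome.
2. Do not waive the documentation condition for events only. Examine incomplete documentation in a set that keeps all treated or all randomised patients, with the same missing-data rule for events and non-events.
3. State that the robustness check for this endpoint refers to the safety-population result and not the ITT result.
4. State what planned therapy covers, so that completion can be judged in the same way at every site.

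Cost: a few sentences, with no added patients or visits. The reason for stopping must be recorded, and its attribution is open to judgement in an open-label trial. Patients who stop for other reasons would still leave the revised per-protocol set, so it should be read beside the analysis in item 2 and not in place of it.

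### The population used for the primary endpoint does not keep switched patients in their randomised arm: depending on how "planned therapy" is read, they are excluded or moved to the other arm

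*Protocol article*

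**What the plan says.** All of the relevant rules stand in the second paragraph of the protocol article's Statistical considerations.

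- **ITT population:** "The ITT population comprises all randomized patients which are evaluated in the treatment arm to which they were randomized". It is the primary population for efficacy endpoints and patient characteristics.
- **Per-protocol population:** ITT patients "who received the planned therapy in its entirety and for whom documentation is complete with respect to the primary endpoint". Its analyses are sensitivity analyses, "which will be used to investigate the robustness of the results from the ITT analysis".
- **Safety population, entry:** "All patients in the ITT population in whom the planned therapy was started (at least 1 day) belong to the safety population".
- **Safety population, arm:** patients "will be evaluated in the therapy arm to which they were treated".
- **Role of the safety population:** "This is the primary evaluation population for the primary endpoint as well as for all other safety endpoints".

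The preceding paragraph of the same section says that secondary variables are evaluated descriptively. The test of the primary endpoint is therefore the only confirmatory one. On where treatment is given, Target volume delineation and radiotherapy application says: "Photon radiotherapy is performed in all participating centers, while proton beam radiotherapy is performed at the Heidelberg ion beam therapy center" or at the Marburg facility.

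**The concern.** The safety rule uses two different criteria. Entry depends on the planned therapy having been started; arm depends on the therapy received. The article does not say whether the planned therapy is the modality to which the patient was allocated or study radiotherapy in general, and a patient who gets the other modality from the first fraction is handled differently under each meaning.

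This matters because the set carries the superiority test of a randomised, open-label trial. A switch happens after randomisation, with the arm known, and may be related to the patient's condition. If switchers have a different toxicity risk from other patients, removing them from one arm or adding them to the other creates a difference that the treatment did not cause. Protons are available at two facilities and photons at every centre, so switching out of the proton arm is plausibly the commoner direction. If the patients who leave are at higher risk, the proton arm then looks better than it is.

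**Working it through.** **Reading the rule**

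Take a patient randomised to protons and given photons from day 1.

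| Meaning of planned therapy | In the safety set? | Arm in the primary analysis |
|---|---|---|
| Allocated modality | No, it was never started | None |
| Study radiotherapy of either kind | Yes | Photon |

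The per-protocol sentence supports the first meaning: if planned therapy there meant either modality, a complete crossover would count as per-protocol. The as-treated clause supports the second, because under the first it could reach only patients who began the allocated modality and changed later. Neither row keeps the patient in the proton arm.

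**The plan's own figure**

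Inputs from Statistical considerations: 21% photon, 9% proton, one-sided α = 0.025, power 80%, chi-square test, 15% dropout. With mean rate 0.15:

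n = [1.960·√(2·0.15·0.85) + 0.842·√(0.21·0.79 + 0.09·0.91)]² / 0.12² = 137.8, so 138 per group. The power at 138 is 80.06%. Then 138/0.85 = 162.4, so 163 per group and 326 in total. The stated sample size reproduces and is not in question.

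**Error rate with no true effect**

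Assumptions, none of them from the documents: both randomised arms have a true rate of 21%; 7 of 138 proton patients (5%) receive photons from the start; nobody switches the other way; switchers' own toxicity risk r is 30% or 50%. The unadjusted test is used, as in the sample-size calculation.

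Rejection probability = Φ[(difference − 1.960·s₀)/s₁], where s₀ is the pooled and s₁ the unpooled standard error. The randomised proton arm has 138 × 0.21 = 28.98 expected events.

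- Excluded, r = 30%: proton rate (28.98 − 2.10)/131 = 0.2052 against 0.2100. Rejection 3.1%.
- Excluded, r = 50%: proton rate (28.98 − 3.50)/131 = 0.1945 against 0.2100. Rejection 5.0%.
- Counted as photon, r = 30%: 0.2052 against (28.98 + 2.10)/145 = 0.2143. Rejection 3.8%.
- Counted as photon, r = 50%: 0.1945 against (28.98 + 3.50)/145 = 0.2240. Rejection 8.6%.
- Randomised arm: 0.21 against 0.21. Rejection 2.5%.

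**Power at the planned effect, switchers not selected**

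Switchers are taken to have the photon rate of 21%. In the randomised arm with 7 switchers, the proton rate becomes (131 × 0.09 + 7 × 0.21)/138 = 0.0961.

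| Switched out of protons | Excluded | Counted as photon | Randomised arm |
|---|---|---|---|
| 3 (2%) | 79.6% | 79.9% | 78.0% |
| 7 (5%) | 78.9% | 79.7% | 75.1% |
| 14 (10%) | 77.5% | 79.1% | 69.6% |

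**The case against.** The strongest reply is that a safety population analysed as treated is ordinary for a toxicity endpoint, and that planned therapy can be read as study radiotherapy of either kind. The rule is then coherent: the switched patient is included and counted under the treatment received. This disposes of any claim that the article states that such patients are dropped. A reader might infer that from the per-protocol wording, but it is one reading and not a stated rule. The reply does not restore the randomised comparison, because on this reading the patient changes arm.

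A reader might also object that no arm is named for a patient who changes modality mid-course. That is true of the text, but it is a detail that a condensed article commonly leaves to the full protocol or the analysis plan, and it is not an error by itself.

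The size is open to challenge too. The documents report no switches and expect no particular rate. Two of the three named locations correspond to the proton facilities, so the direction of switching is an inference. Examples close to the threshold can be made to look dramatic. With assumed counts of 17/138 proton and 29/138 photon, one-sided p = 0.026. Excluding four proton patients who all had events gives 13/134 against 29/138, p = 0.005. If none of the four had events, 17/134 against 29/138 gives p = 0.033. The result depends on who switches, and the documents do not support the extreme case. If switchers had a lower risk than other patients, the bias would run against protons.

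Finally, the per-protocol sentence refers to an ITT analysis, so an analysis of this endpoint by randomised arm may be intended. The article nevertheless gives the primary role to the safety set.

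**Conclusion.** The point holds as a defect in a rule that the article states. The set for the only confirmatory test has an entry condition with two possible meanings and assigns patients by treatment received. A patient given the other modality from day 1 is excluded on one meaning and moved on the other.

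The size in this trial is unknown. With 5% one-way switching and a switcher risk of 30–50%, the one-sided error is about 3–5% if switchers are excluded and about 4–9% if they are counted as photon, against 2.5% by randomised arm. With no switching there is no effect from this source. These figures use the unadjusted test; the planned logistic regression adjusts for fractionation, subventricular zone involvement and concurrent chemotherapy, and would remove the bias only as far as those factors explain the switchers' risk. The sample size stands. The rule should be corrected before the primary analysis.

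**What to change.** For the primary endpoint, define the primary analysis set as every randomised patient who received at least one fraction of either study radiotherapy, and analyse each in the randomised arm, including patients switched before or during the course. The arm must be stated explicitly: if only the entry condition is widened, the existing as-treated clause would still move patients who switched before the first fraction. Define planned therapy where the per-protocol set uses it, and name the analysis that the per-protocol results are meant to check.

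Keep the as-treated analysis as supportive. List all switchers with date, reason and fractions per modality.

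The change needs a few sentences in the population definitions and the fraction counts by modality from the treatment records. The statistical cost is dilution: 5% unselected switching out of protons lowers power from about 80% to about 75%, and 10% lowers it to about 70%, at 138 evaluable patients per group.
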